### Randomisation

Researchers will be assigned to one of the study groups by stratified randomization based on the center and the type of health professional (GP/nurse) using EPIDAT 3.1 software [29].

### Interventions and comparative analysis

**-** EG: All patients seen by the health professionals involved in the present study will undergo active screening for AF, regardless of the reason of their visit. Therefore, the health professional will adopt a “proactive” attitude of opportunistic case finding, either because the professional identifies “silent” AF cases, or because screening for AF was performed, while the patient presented AF-associated symptoms, signs or pathologies.

-CG: Any patient presenting AF-accompanying symptoms (dyspnea, chest pain, palpitations or dizziness) or AF-induced sequels (stroke, transient ischemic attacks, peripheral embolism, heart failure or other associated health disorders) will be eligible. Once the practitioner identifies any of these symptoms, they will perform a screening for AF by measuring the patient’s blood pulse.

### Measurement Instruments and action program

1. A Data Collection Form (DCF) and a Procedure Manual including a Clinical Protocol based on an updated Practice Guideline will be designed [30].

2. A pilot study has already been conducted on a sample of 20 randomized patients in five health centers located in Barcelona and Córdoba, where five GP and five nurses participated. The target population was willing to undergo the test. The data collected by the DCF allowed practitioners to identify two cases of undiagnosed asymptomatic AF.

3. Communication Plan and Recruitment of Health Professionals: the project managers of the study were in charge of the dissemination of the study; in addition, a presentation of the study was performed in different health centers in Barcelona, Córdoba and Badajoz. A total of 269 health professionals at 28 health centers agreed to participate in the study (162 GPs and 107 nurses).

4. Training Plan. A presentation will be given to familiarize the participating practitioners with the study protocol. All participants will take an on-line course on how to approach patients with AF (http://www.semfyc.es/pfw_files/cma/Agenda/Sesiones_multimedia/Documentos/Diptico_referentes_fa.pdf). On the first stage, we intend to designate a practitioner as the expert in FA. The practitioner selected will take an online course to acquire the abilities and skills necessary to be able to give a training session to his/her partners.

### Measurements and Variables

The variables measured are shown in Table 1.

**Table 1 T1:** Variables of the Study

**Variables**	**Definition**	**Measure scale**
**Independet**		
-Study Groups	EG: Opportunistic detection of AF	Dichotomous Qualitative
	CG: regular approach	
-Practitioner	Physician vs. Nurse	Dichotomous Qualitative
**-Sociodemographic:**		
Age	≥ 65 years	Quantitative Discrete
Sex	Man/woman	Dichotomous Qualitative
Marital Status	bachelor, married, widow/er, divorced	Qualitative Polytomous
Residence	Urban (≥ 10.000 population)/Rural (<10.000 population)	Dichotomous Qualitative
**-Clinical and Functional Assessment:**		
Symptoms and Signs	Asymptomatic, Palpitations, Chest Pain, dispnoea, fatigue, diziness, embolism complications or exacerbation of heart failure, weight loss, diarrhea.	Polytomous Qualitative
Conditions (comorbidity) and associated health disorders	High blood pressure, heart disease, mitral stenosis, mitral regurgitation, hypertrophic cardiomyopathy, pericarditis,congenital heart disease, previous cardiac surgery, lung diseases (pneumonia, lung cancer, pulmonary embolism, sarcoidosis), alcohol abuse, hyperthyroidism, bone and joint disorders, neurological, hearing, vision, feet, psychic, digestive, urinary, sleep disorders, other.	Polytomous Qualitative
	To classify chronic disorders we will use the electronic version of the *Second International Clasiffication of Primary Care* (ICPC-2-E) [31]	
Family History of AF	Parents, siblings, children	Polytomous Qualitative
Drug Consumption for Cardiovascular Disease	Name of the drug: The Anatomical Therapeutic Classification (AT) developed by the European Pharmaceutical Market Research Association (EPhMRA) [32]	Polytomous Qualitative
Number of Drugs	Drugs currently consumed	Discrete
		Quantitative
**Dependent:**		
**Peripheral Blood Pulse**	Radial pulse measuring according to the protocol: Regular/Irregular	Dichotomous Qualitative
**Atrial Fibrillation**	ECG according to the clinical protocol	Dichotomous Qualitative
Treatment	Pharmacological (Antiarrhythmic / Anticoagulation)/Non-pharmacological (Cardioversion)	Polytomous Qualitative

### -Statistical Analysis

Statistical analysis will be performed with the statistics analysis software EPIDAT 3.1 [29], SPSS [33], and WLwiN 2.02 [34]. It will include:

a. Descriptive Analysis: characteristics of the population under study (sociodemographic variables): central tendency, dispersion and position measures for quantitative variables; and tabulation and calculation of relative frequencies for qualitative variables. A calculation of major estimators with their corresponding 95% confidence intervals (CI95%) will be performed.

b. Bivariate Analysis: We will examine basal comparability between the two groups using the chi-square test or Fisher’s test (proportion comparison test), or by Student’s t-test (mean comparison test after testing normal distribution). Then, the AF dependent variable will be examined and crossed with the sociodemographic variables and other independent or prognostic variables of interest. On such purpose, we will use Pearson’s chi square tests or Fisher’s test (qualitative variables), and Student’s t-test or ANOVA (quantitative variables). All contrasts will be bilateral (p < 0.05).

c. Analysis of the relationship between the type of intervention and the primary variable of the study (AF): contingency tables, square chi test, relative risk estimation), attributable risk and number of subjects to be treated, with their respective CI95%.

d. Multivariate Analysis: A multi-level logistic regression or multiple logistic regression will be performed to compare effects of the strategy on both groups (Odds Ratio) adjusting the model for potential prognostic and / or confounding candidate variables. When multiple logistic regression is used, these variables will be introduced by the “Enter” technique. Significance will be > 0.10 according to Wald’s test.

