## Background

Atrial fibrillation (AF) is defined as a cardiac arrhythmia involving irregular atrial activation, uncoordinated atrial systole and ineffective ventricular filling. ECG shows no P wave but displays fast fibrillation waves different in form, size and rhythm that lead to an irregular ventricular response. Echocardiogram shows no mitral A wave valvular movement [1]. AF is the most frequent arrhythmia in clinical practice and a growing challenge to public health due to population aging. The estimated prevalence of AF is 0.4-1% in the general population and increases with age up to 5-6% in the population aged > 65 years, and 8% in subjects aged 80 years or older [2,3]. Similarly, while the incidence of AF is < 0.1% per year in subjects aged < 40 years, it increases to above 1.5% per year in women and 2% in men aged > 80 years [4]. The incidence of AF was expected to increase 5-fold by the year 2010 [5-8]. According to the Framingham Heart Study, lifetime risk for AF is 1 in 4 in men and women aged 40 years or older. Lifetime risks remain greater even in absence of congestive heart failure or myocardial infarction (1 in 6) [9]. AF is one of the fastest-growing cardiovascular epidemics of the 21^st^ century, as it is one the major causes of morbidity and mortality, and it increases death risk, congestive heart failure and the risk for embolisms –including strokes [6,10-12]. One in every six strokes occur in subjects with AF [13,14], and the increased risk for ictus depends on the number of additional risk factors. In addition, the quality of life of these patients is severely impaired, mainly due to their inability to perform daily activities as a result of the risk of exacerbation of symptoms [15]. Over the last 20 years, admissions for AF have increased by 66% as a result of population aging, the increasing prevalence of chronic heart diseases, the more frequent diagnosis by ambulatory control mechanisms, and other factors [16].

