### Research objectives

The three main aims of this study are:

To establish the percentage of patients with AF identified “de novo” by radial pulse assessment as compared to those discovered by regular clinical practice.

To know the amount of asymptomatic AF patients, and the symptoms and clinical signs showed by symptomatic AF patients.

To identify the different AF typologies following expert panels’ classifications.

Complementary objectives are:

To know the socio-demographics of the population with AF.

To identify health problems associated with this condition (comorbidity and risk factors).

To know the previous treatment followed by these patients.

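### The objective on health problems associated with AF has only unadjusted tests at p<0.05 behind it, so age and study group can distort the associations reported (minor)

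*Protocol article*

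**What the plan says.** Research objectives, complementary objectives: "To identify health problems associated with this condition (comorbidity and risk factors".

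Table 1 records these health problems in one row, scaled as polytomous. It runs from "High blood pressure, heart disease, mitral stenosis, mitral regurgitation, hypertrophic cardiomyopathy, pericarditis,congenital heart disease, previous cardiac surgery, lung diseases" to "bone and joint disorders, neurological, hearing, vision, feet, psychic, digestive, urinary, sleep disorders, other". Age (quantitative), sex and study group are also in Table 1.

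Statistical Analysis, item b, is the only item that relates AF to these variables: "Then, the AF dependent variable will be examined and crossed with the sociodemographic variables and other independent or prognostic variables of interest". The tests are named: "we will use Pearson’s chi square tests or Fisher’s test (qualitative variables), and Student’s t-test or ANOVA (quantitative variables". So is the threshold: "All contrasts will be bilateral (p < 0.05". No adjustment or stratification is stated for these comparisons.

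Item d describes a multilevel or multiple logistic model for AF. Its stated purpose is "to compare effects of the strategy on both groups (Odds Ratio) adjusting the model for potential prognostic and / or confounding candidate variables".

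The Background says that AF prevalence "increases with age up to 5-6% in the population aged > 65 years, and 8% in subjects aged 80 years or older".

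**The concern.** AF depends on age within the population being recruited. If a listed condition also becomes more frequent with age, patients with AF will have it more often simply because they are older. An unadjusted chi-square or Fisher test cannot separate this from a real link. Hearing, vision, foot, joint and urinary disorders are plausible candidates.

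Study group is a second source of distortion. Under Interventions, control patients become eligible by presenting with symptoms or sequels such as stroke or heart failure, while experimental patients are screened whatever the reason for the visit. The Sample size section expects different AF rates in the two groups. A table that pools the groups therefore mixes the effect of group with that of the condition.

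At stake is what the trial publishes about AF comorbidity and risk factors. A marker of age could be presented as a risk factor, or a real association could be weakened.

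**Working it through.** The article gives no figure for this analysis, so there is none to reproduce. Its sample sizes are consistent on inflation: 7 722/0.90 = 8 580 and 3 861/0.90 = 4 290. I use the sizes before inflation, 7 722 + 3 861 = 11 583.

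**Expected new AF cases** (Sample size section)
- Experimental: 7 722 × 1.63% = 125.9
- Control: 3 861 × 1.012% = 39.1
- Total: about 165, or 165/11 583 = 1.424%

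**Confounding by age**

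From the Background: 8% AF at 80 or older, and 5.5% overall (midpoint of 5-6%).

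Assumptions not in the documents:
- a share s = 20% to 35% of patients is aged 80 or older;
- the condition is present in c = 10% to 30% of those aged 65-79, and 20 points more often at 80 or older;
- there is no link with AF within either age band;
- the age ratio for prevalent AF also holds for newly found AF.

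AF at 65-79 = (5.5% − s × 8%)/(1 − s):
- s = 20%: 4.88%, ratio of 80+ to 65-79 = 1.64
- s = 35%: 4.15%, ratio = 1.93

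Share aged 80+ among AF cases = s × 8/5.5. Among non-cases it is (s − 0.01424 × that share)/(1 − 0.01424).
- s = 20%: 29.1% against 19.9%
- s = 35%: 50.9% against 34.8%

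Frequency of the condition = c + 0.20 × share aged 80+. The two extremes of the grid are:

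| s | c | In AF cases | In non-cases | Crude OR |
|---|---|---|---|---|
| 20% | 30% | 35.8% | 34.0% | 1.085 |
| 35% | 10% | 20.2% | 17.0% | 1.239 |

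Chance of p<0.05 = Φ(δ/SE − 1.96) + Φ(−δ/SE − 1.96), where δ is the difference in frequency, SE = √[p(1−p)(1/165 + 1/11 418)], and p is the pooled frequency.
- First row: δ = 0.0184, SE = 0.0371, ratio 0.50; chance 7.9%
- Second row: δ = 0.0323, SE = 0.0295, ratio 1.10; chance 19.5%

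Using the unpooled standard error for the spread of the difference gives 8.2% and 21.1%, so the result does not hang on the approximation.

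A wider set of assumptions (15-35% aged 80+, a condition in 20-25% below 80 and 35-50% at 80+, overall AF of 5% or 6%) gives crude odds ratios of about 1.03 to 1.35. The chance of p<0.05 in the direction of the bias is then about 4% to 46%. Two age bands are coarse, and a finer age gradient could make the confounding larger.

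**Mixing of study group**

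Illustration, with assumed frequencies: a condition in 20% of experimental and 40% of control patients, with no link to AF in either group.
- Among AF cases: (125.9 × 0.20 + 39.1 × 0.40)/165 = 24.7%
- Among non-cases: (7 596 × 0.20 + 3 822 × 0.40)/11 418 = 26.7%
- Pooled crude OR = (0.247/0.753)/(0.267/0.733) = 0.90

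Here the distortion runs against a positive association, so the two effects need not point the same way.

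**The case against.** The objective is complementary. It stands between knowing the socio-demographics of patients with AF and knowing their previous treatment, so it can be read as descriptive. A crude table is a legitimate description of which conditions accompany AF. This stands in part: only the mention of risk factors, together with the p<0.05 rule, takes the objective beyond description.

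Item d is a multivariable model for AF and could give age-adjusted coefficients for any condition entered. That is possible but not planned: the covariates are unnamed, the stated use is the strategy odds ratio, and nothing says other coefficients will be reported.

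An article may leave detail to a full protocol or analysis plan. That covers multiplicity rules and covariate lists. It does not cover this point, because the article itself names the test and the threshold.

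Three stronger readings are tempting, and the documents support none of them:
- *Age-related disorders will be reported as linked to AF.* On the main assumptions each such condition misses p<0.05 about 80 to 92% of the time, and the documents give no age gradient for any condition.
- *About 21 conditions tested at 0.05 give a 66% chance of a false finding (1 − 0.95^21).* This needs 21 independent tests, all truly null. Table 1 has a single polytomous row, item b does not promise a test for every entry, and the list includes plausible true correlates such as heart disease and mitral stenosis.
- *The bias is much larger because prevalent AF cases add hundreds of events.* The Participants section says these patients will be described as existing cases. It does not say that they enter item b.

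**Conclusion.** The concern holds as a minor weakness. The only analysis stated for the comorbidity and risk-factor objective is unadjusted, although the article itself says AF rises with age and builds in a difference between the groups in who enters and in the expected AF rate.

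With about 165 new cases, confounding by age alone gives a crude odds ratio of about 1.1 to 1.2 and a chance of p<0.05 of about 8 to 20% per age-related condition, where 5% is intended. These figures rest on the assumed age mix and the assumed 20-point rise in the condition. The group effect likewise depends on assumed frequencies and on item b pooling the arms, which it does not rule out. The primary comparison and the sample size are not affected.

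**What to change.** In item b, state that for each condition an odds ratio for AF adjusted for age (continuous), sex and study group will be reported with its 95% CI, beside the crude table. Label these results exploratory and do not judge each at p<0.05.

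If only description is intended, remove the reference to risk factors from the objective and exempt it from the p<0.05 rule.

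Either change is a matter of wording. The first adds a few logistic models on variables already in Table 1, and some associations may weaken. A formal multiplicity correction or a practitioner random effect in each model would be optional for secondary work of this kind.

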### Sample size

The primary endpoint will be the percentage of AF cases; sample size estimation was performed according to the results obtained by Fitzmaurice DA [25] in its trial of effectiveness, using EPIDAT 3.1 software [29] and within the following criteria:

Risk in exposed patients: 1.63%; risk in non-exposed: 1.012%, expected relative risk: 1.62%.

Controls –CG– per case –EG–: 0.5 (1:2 ratio). With this ratio, we intend to optimize and make the study feasible, as it will be more difficult to identify and recruit controls.

Confidence level: 95.0%; accuracy: 80%; the resulting sample size is 7 722 subjects for the EG, and 3 861 subjects for the CG. As we estimated a non-response rate of 10%, we adjusted the formula Nf= Ni [1/(1-R)]=7 722 [1/(1-0,10)]= 8 580 (GE) and del GC= Ni [1/(1-R)]=3 861 [1/(1-0,10)]= 4 290. Consequently, the total N= 8 580 + 4 290=12 870 subjects. As this is a cluster design study and according to the study referenced above [25], at least 100 health professionals should recruit at least 12 000 patients. Since the probability of finding patients meeting the eligibility criteria is much lower for the CG than for the EG, stratified randomization will be used to assign at least 200 primary care health professionals to the two groups, with a 2:3 ratio. In other words, there will be three CG health practitioners for every two EG practitioners.

Patient selection will be performed by consecutive sampling.

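### The RR, attributable risk and NNT for AF come only from a pooled table that ignores the randomisation strata, and the adjusted model does not commit to those strata

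*Protocol article*

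**What the plan says.** The Randomisation section of the protocol article allocates professionals by "stratified randomization based on the center and the type of health professional (GP/nurse"). Under Measurement Instruments there are 269 professionals at 28 centres: 162 GPs and 107 nurses. The Sample size section adds that "there will be three CG health practitioners for every two EG practitioners", while the planned patient numbers run the other way, two EG patients to one CG patient. Patients are taken consecutively.

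Item c of the Statistical Analysis section is the arm comparison on AF: "Analysis of the relationship between the type of intervention and the primary variable of the study (AF): contingency tables, square chi test, relative risk estimation". To these it adds the attributable risk and an NNT, each with a 95% confidence interval. No stratification or adjustment is mentioned. Item d is a second arm comparison: "A multi-level logistic regression or multiple logistic regression will be performed to compare effects of the strategy on both groups (Odds Ratio"). Its only statement on covariates is "adjusting the model for potential prognostic and / or confounding candidate variables"; none of them is named. Table 1 lists type of professional ("Physician vs. Nurse") among the independent variables; it does not list centre.

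**The concern.** The two factors that define the randomisation strata play no part in the only analysis that yields an RR, an attributable risk or an NNT. Stratified allocation fixes how many professionals of each type and centre go to each arm. It does not fix how many patients each of them contributes.

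The plan itself makes unequal contributions likely. The section on interventions has EG professionals screen every patient they see, whereas CG patients qualify only with symptoms or sequels. The trial is open, and control patients are expected to be much harder to find. Nothing keeps that difference in recruitment the same for GPs and nurses, or the same in every centre. If it varies and AF yield varies too, the crude RR and NNT mix the effect of screening with differences between strata. Correcting the crude RR's confidence interval for clustering would leave this bias in place.

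**Working it through.** **The plan's own figures.** The Sample size section gives "Risk in exposed patients: 1.63%; risk in non-exposed: 1.012%, expected relative risk: 1.62" (printed with a percent sign).

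- RR: 1.63/1.012 = 1.611.
- Inflation for non-response: 7 722/0.9 = 8 580 and 3 861/0.9 = 4 290, both exact.
- The 7 722 is reproduced within 3% by standard two-proportion formulas at two-sided 5% and 80% power. The unpooled variance with continuity correction, taking 1.63% and RR 1.62, gives 7 725. The unweighted mean proportion without correction, taking 1.63% and 1.012%, gives 7 847.

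**Recruitment per professional.** At 2:3, the 269 professionals split into 0.4 × 269 = 107.6 EG and 0.6 × 269 = 161.4 CG.

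- EG: 8 580/107.6 = 79.7 patients each.
- CG: 4 290/161.4 = 26.6 patients each.

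The plan therefore expects a threefold difference by arm.

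**Bias of the crude RR.** Let R be the RR within each stratum, r the AF yield in GP patients divided by that in nurse patients, and gE and gC the GP share of patients in each arm. Then

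crude RR = R × (gE·r + 1 − gE)/(gC·r + 1 − gC).

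R = 1.611 is the plan's value. A GP share near 60% matches 162/269 = 0.602. The gaps in share and the values of r are assumptions; the article gives none.

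| r | gE | gC | multiplier | crude RR | bias |
|---|---|---|---|---|---|
| any | 0.6 | 0.6 | 1 | 1.61 | 0 |
| 1.5 | 0.7 | 0.6 | 1.35/1.30 | 1.67 | +3.8% |
| 1.5 | 0.6 | 0.7 | 1.30/1.35 | 1.55 | −3.7% |
| 1.5 | 0.6 | 0.8 | 1.30/1.40 | 1.50 | −7.1% |
| 2 | 0.7 | 0.5 | 1.70/1.50 | 1.83 | +13.3% |
| 2 | 0.5 | 0.7 | 1.50/1.70 | 1.42 | −11.8% |
| 2 | 0.6 | 0.8 | 1.60/1.80 | 1.43 | −11.1% |
| 0.5 | 0.6 | 0.8 | 0.70/0.60 | 1.88 | +16.7% |

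**NNT.** The plan's risks give 1/(0.0163 − 0.01012) = 162. Hold the EG risk at 1.63% with a 60% GP share.

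- r = 1.5, gC = 0.7: CG risk 1.012% × 1.35/1.30 = 1.051%, so NNT = 1/0.00579 = 173.
- r = 2, gC = 0.8: CG risk 1.012% × 1.80/1.60 = 1.1385%, so NNT = 1/0.004915 = 203.

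**Simulation with the stated allocation** (28 centres × GP/nurse, 2:3 within stratum, true RR 1.61). With no arm-related shift in recruitment, the crude RR averages 1.62–1.63, so there is no material bias. If EG GPs recruit 50% more (GP yield 1.5 or 2 times that of nurses), the crude RR averages 1.68–1.71 and the stratified RR 1.61–1.63.

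**Precision.** Treating patients as independent, stratifying on GP/nurse removes under 0.4% of the variance (yield ratio up to 3), and on centre 0.1–1.7% (coefficient of variation of centre risk 0.25–1). In a simulation with a variance that allows for professionals (professional SD 0.3 on the log-risk scale), adding centre terms moves power from 74% to 75%, 71% to 74% and 65% to 71% at centre SDs of 0.3, 0.5 and 0.7. The last is large variation. With no centre variation, 28 fixed centre terms cost about one point.

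**The case against.** Item d is also an arm comparison on AF. It is adjusted and possibly multilevel, and the abstract names multilevel logistic regression. Type of professional stands directly after study group in Table 1, so it is an obvious candidate for the model. An article may leave a covariate list to a fuller document. A reader might infer that the only comparison on AF is unstratified; that is not so, and item c is not declared primary over item d. What remains is that item c states its method outright, and that the RR, attributable risk and NNT appear nowhere else.

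A reader might also infer that the stratification is wasted. It is not: it balances professionals whatever the analysis, and it protects the crude RR when recruitment per professional does not shift between strata by arm.

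Nor do the documents show that the crude RR is biased. They support recruitment that differs by arm, not recruitment that differs by arm between GPs and nurses. That symptomatic patients reach GPs more often is conjecture. A 4% bias is 0.04 on the log scale, small against a simulated standard deviation of log RR of 0.19–0.20; 13% is 0.125, about two thirds of it.

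Finally, item c as written ignores clustering by professional. This is a separate and probably larger defect: with assumed intracluster correlations of 0.005 to 0.05, the type I error of the naive chi-square is about 7% to 25%.

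**Conclusion.** The point holds as a weakness in a stated method. The crude RR, attributable risk and NNT are open to bias from the mix of patients by centre and GP/nurse, and no analysis in the article is committed to removing it. Bias needs two conditions together: a patient mix that differs between arms, and an AF yield that differs between strata. The first is plausible from the plan's recruitment rules; neither is established. On the assumed inputs the size runs from nil with equal shares, through about 4%, to about 11–13% at a 20-point gap and yield ratio 2. One assumed case with the yield ratio reversed reaches 17%. Lost precision is a minor consideration.

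**What to change.** Make the main arm comparison the multilevel logistic model already named in item d, and drop ordinary logistic regression as an equal alternative. Professional is a random effect, arm and GP/nurse are fixed effects, and centre is a random effect. State that centre and GP/nurse are always in the model and are not candidate variables. Derive the RR, risk difference and NNT from it, for example by standardisation, with confidence intervals that allow for clustering by professional. Keep the pooled table as descriptive.

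A Mantel-Haenszel RR over centre × GP/nurse should be a sensitivity analysis at most, with a variance that allows for clustering. There are up to 28 × 2 = 56 strata, about 269/56 = 4.8 professionals in each, and 3 861 × 0.01012 = 39 expected control events in all, under one per stratum. Its usual variance also treats patients as independent.

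The cost is wording and slightly more analysis work: both factors are known at randomisation and multilevel software is already listed. At most about one point of power is lost if centres do not differ, and a random centre effect should limit that. The change does not restore comparability lost through the symptom-based selection of control patients within strata.

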**Methods/design:**

An cluster-randomized controlled trial conducted in Primary Care Centers of the Spanish National Health Service. A total of 269 physicians and nurses will be allocated to one of the two arms of the trial by stratified randomization with a 3:2 ratio (three practitioners will be assigned to the Control Group for every two practitioners assigned to the Experimental Group). As many as 12 870 patients aged 65 years or older and meeting eligibility criteria will be recruited (8 580 will be allocated to the Experimental Group and 4 290 to the Control Group). Randomization and allocation to trial groups will be carried out by a central computer system. The Experimental Group practitioners will conduct an opportunistic case finding for patients with Atrial Fibrillation, while the Control Group practitioners will follow the regular guidelines. The first step will be finding new Atrial Fibrillation cases. A descriptive inferential analysis will be performed (bivariate and multivariate by multilevel logistic regression analysis).

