## Methods/design

### Design of the study

A open, cluster, multicenter, two-arm, individual randomization, controlled trial of the efficacy of performing opportunistic screening versus regular clinical practice (Figure 1).

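### Practitioners are randomised, but the stated comparison on the primary variable names no adjustment for clustering, and the regression section lets an ordinary logistic model replace the multilevel one with no rule for choosing

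*Protocol article*

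**What the plan says.** - **Unit of allocation.** The Randomisation section states: "Researchers will be assigned to one of the study groups by stratified randomization based on the center and the type of health professional (GP/nurse"). The Sample size section also allocates practitioners: "there will be three CG health practitioners for every two EG practitioners". The abstract describes "An cluster-randomized controlled trial conducted in Primary Care Centers of the Spanish National Health Service". Under Design of the study the label is "A open, cluster, multicenter, two-arm, individual randomization, controlled trial", which puts cluster and individual randomisation into one phrase.
- **Number of clusters.** "A total of 269 health professionals at 28 health centers agreed to participate in the study (162 GPs and 107 nurses"). The Sample size section requires at least 200.
- **Analysis of the primary variable.** Statistical Analysis item c relates the type of intervention to the primary variable, AF, through "contingency tables, square chi test, relative risk estimation), attributable risk and number of subjects to be treated, with their respective CI95". No method that allows for practitioner is named.
- **Regression.** Item d begins: "A multi-level logistic regression or multiple logistic regression will be performed". It then describes how variables enter if the ordinary model is used, but not when that model would be used. The abstract mentions multilevel logistic regression only.
- **ICC.** No ICC or design effect appears anywhere. The Sample size section notes that the design is clustered and takes minimum numbers of professionals and patients from the reference trial.

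**The concern.** A chi-square test on a patient-level table, with the usual intervals, assumes independent patients. Here one professional finds the patient and takes the pulse. The section on protection against bias itself expects AF identification on the ECG to depend on practitioner skill, and it plans to examine interobserver agreement. Some positive correlation within practitioner is therefore plausible.

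If it exists and is not allowed for, standard errors are too small, the test rejects a true null more often than 5%, and the intervals for relative risk, attributable risk and number needed to treat are too narrow. The sponsor hopes the result will enter practice guidelines, so these are the figures that readers would use. Because item d leaves the model open, two analysts who both follow the plan could report different precision for the same data.

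**Working it through.** **1. The plan's sample size.** Inputs (Sample size section): risks 1.63% and 1.012%, relative risk 1.62, EG:CG 2:1, 95% confidence, 80% (printed as accuracy, read as power). The article does not give the formula. The closest match found is the arcsine formula with EG risk 0.01012 × 1.62 = 0.016394:

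- h = 2·asin√0.016394 − 2·asin√0.01012 = 0.05525
- n(CG) = (1.960 + 0.842)² × 1.5 / h² ≈ 3 857, so n(EG) ≈ 7 714

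The plan states 3 861 and 7 722. Some other variants also come within 3%; the usual pooled formula gives 4 136 and 8 272, about 7% higher. The non-response step is exact: 7 722/0.9 = 8 580 and 3 861/0.9 = 4 290. All these formulas treat patients as independent, so the stated N contains no visible allowance for clustering.

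**2. Cluster sizes.** 269 practitioners at 3 CG : 2 EG give 269 × 3/5 ≈ 161 and 269 × 2/5 ≈ 108. Mean sizes are 8 580/107.6 = 79.7 (EG) and 4 290/161.4 = 26.6 (CG).

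**3. Variance inflation and actual error of a patient-level test.** The ICC is assumed, over a range.

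- Design effect per arm: DE = 1 + (m − 1) × ICC
- V = (DE_E/N_E + DE_C/N_C) / (1/N_E + 1/N_C), which is (DE_E + 2·DE_C)/3 when N_E = 2·N_C
- Actual two-sided error = 2 × [1 − Φ(1.96/√V)]

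At ICC 0.01: DE_E = 1 + 78.7 × 0.01 = 1.787; DE_C = 1 + 25.6 × 0.01 = 1.256; V = (1.787 + 2.512)/3 = 1.433; 1.96/√1.433 = 1.637; error 10.2%.

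**4. Power of an analysis that respects clustering, N = 12 870.** With pooled risk p̄ = (2 × 0.0163 + 0.01012)/3 = 0.01424:

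- s0 = √[p̄(1 − p̄)(DE_E/N_E + DE_C/N_C)]
- s1 = √[p_E(1 − p_E)DE_E/N_E + p_C(1 − p_C)DE_C/N_C]
- power = Φ[(0.00618 − 1.96·s0)/s1]

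At ICC 0.01: s0 = 0.002652, s1 = 0.002505, power = Φ(0.392) = 65%.

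| Assumed ICC | DE_E | DE_C | V | Error of patient-level test | Coverage of nominal 95% CI | Power, clustering respected |
|---|---|---|---|---|---|---|
| 0 | 1.00 | 1.00 | 1.00 | 5.0% | 95% | 81.5% |
| 0.001 | 1.08 | 1.03 | 1.04 | 5.5% | 94.5% | 79.7% |
| 0.005 | 1.39 | 1.13 | 1.22 | 7.6% | 92.4% | 72.8% |
| 0.01 | 1.79 | 1.26 | 1.43 | 10.2% | 89.8% | 65.3% |
| 0.02 | 2.57 | 1.51 | 1.87 | 15.1% | 84.9% | 53.4% |
| 0.05 | 4.94 | 2.28 | 3.17 | 27.1% | 72.9% | 34.3% |

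A beta-binomial simulation with 20 000 replicates gave errors of 5.0, 5.4, 7.4, 10.1, 15.1 and 26.7%.

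**5. Sensitivity.** With the minimum of 200 practitioners (about 107 and 36 patients each), the errors from ICC 0.001 upwards are 5.7, 8.5, 12.0, 18.4 and 32.3%. If cluster sizes vary (assumed coefficient of variation 0.6, 269 practitioners), the error at ICC 0.01 is 12.0%. If 10% of patients are lost as planned (7 722 and 3 861 remain), it is 9.6%, and power with clustering respected is 62%.

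**6. Plausibility of the upper end.** At a common rate of 1.42%, ICC 0.05 implies a between-practitioner SD of √(0.05 × 0.0142 × 0.9858) = 2.6 percentage points, nearly twice the mean. At ICC 0.01 it is 1.2 points.

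**The case against.** The strongest reply is that the plan does provide for clustering. The abstract commits to multilevel regression, item d names the multilevel model first, and the software list appears to include a multilevel package. That stands. A reader might infer that the trial ignores clustering; the documents do not support this. They make the valid analysis optional.

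Other stronger readings also fail or need a condition:

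- **That the crude chi-square is the primary analysis.** No analysis carries that label. Item c is tied to the primary variable, but item d also compares the strategies. What is fixed badly is that nothing says which one decides.
- **That the intervals in item c are certainly the ordinary ones.** No variance method is given. Ordinary intervals are the natural reading, but not a stated fact.
- **That the false-positive rate exceeds 5% whatever the data.** This needs a positive ICC. At 0.001 the excess is half a percentage point.
- **That leaving out centre adds to the error.** Randomisation is stratified by centre, so centre is balanced across arms. Omitting such a stratum generally makes the test conservative; adjusting for it is a matter of precision.
- **That patients are individually randomised.** The label under Design of the study can be read as individual practitioners being randomised rather than centres, and the Randomisation section settles the unit. It is a wording defect and does not bear on the error rate.

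A fuller analysis plan might settle the choice of model. That does not remove the disagreement between the abstract and item d, or the absence of any adjustment where item c lists its methods.

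**Conclusion.** The point holds in this limited form. The methods listed for the primary variable do not match the unit of randomisation, and the article disagrees with itself on whether the regression must be multilevel. For any positive practitioner-level ICC, a patient-level test and its intervals overstate precision. The direction is certain on that condition; the size is not, because no ICC is given. Across assumed values from 0.001 to 0.02 the actual error runs from about 5.5% to 15%. The 27% at ICC 0.05 should carry little weight at so low an event rate. The main table assumes equal cluster sizes within arm, 269 practitioners split 3:2, and all 12 870 patients contributing data. The plan should settle this before any comparison by arm is made.

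**What to change.** - Name one primary analysis: a mixed-effects logistic model, or GEE with robust standard errors, with practitioner as the cluster and arm as a fixed effect. Adjust for the randomisation strata (professional type and centre) for precision.
- Obtain the relative risk, risk difference and number needed to treat with cluster-adjusted intervals, from that model by averaging predicted risks or by a cluster-robust variance. Keep the crude table as description.
- Delete the ordinary logistic alternative from item d, so that it agrees with the abstract.
- Align the design label with the Randomisation section: practitioners are the randomised unit.
- Restate the power in the Sample size section with an assumed ICC and its basis.

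**Cost.** The analysis changes are wording, and multilevel software appears to be listed already. The intervals become wider: at ICC 0.01 the standard error grows by √1.433 = 1.20, about 20%. Power at 12 870 patients is about 80%, 73%, 65% and 53% at ICC 0.001, 0.005, 0.01 and 0.02. From about 0.005 upwards the trial is clearly below its stated 80%, and the sponsor should decide knowingly whether to accept that or revisit the sample size.
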